### Study Setting

The study will be undertaken at Brightwater Care Group (“Brightwater”), a large postacute, residential, and community-based aged care and disability service in Perth, Western Australia. Brightwater provides residential and home-based care for approximately 1882 aged care and 522 disability services clients across 10 different programs (Table 2).

**Table 2 table2:** Overview of aged care and disability services.

Service type and program name		Sites, n	Clients, n	Description

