##### Phase 1.2: Measure

The measure phase will focus on measuring the baseline (T_0_) quality of clinical data across services and identifying key data quality issues. T_0_ data quality will be measured through an audit of client EHRs using a 6-month lookback period. Data quality will be measured in terms of the *number of defects* present in EHRs, measured using the CTQ metrics identified by the expert group.

Specifically, T_0_ data quality will be measured by the number of defects per unit (DPU), defects per opportunity (DPO), defects per million opportunities (DPMO), and the Sigma level (Table 4). T_0_ data quality will be measured for each of the 8 programs to allow the identification of any systematic variation between sites and service-specific data quality issues. In addition, the assessment will identify the most common types of defects across services to inform system optimization.

**Table 4 table4:** *Six Sigma* metrics for measuring defects.

Metric	Formula	Description
DPU^a^		Measures the average number of defects present in a unit (ie, the average number of defects in each client EHR^b^)
DPO^c^		Measures the number of defects as a proportion of the total number of data fields (ie, opportunities) present in each client EHR
DPMO^d^		Measures the number of DPO expressed per million
Sigma level	Determined from conversion tables using calculated DPMO	Measures the amount of variability in a process. *Six Sigma* quality performance is defined as 3.4 DPMO.

^a^DPU: defects per unit.

^b^EHR: electronic health record.

^c^DPO: defects per opportunity.

^d^DPMO: defects per million opportunities.

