#### Stage 3: Evaluation

The final stage of the study will evaluate changes in the primary and secondary outcomes in the 12 months following the full optimization (Table 5). Outcomes will be measured at T_0_ and at 1, 3, 6, 9, and 12 months after full optimization. Previous studies in Australian RACFs have shown that the time spent on documentation tasks generally increases in the period after the implementation of new or changed systems as users learn the new technology and adjust their workflows [11,12]. Therefore, long-term evaluation is critical for reliably quantifying changes in outcomes and their impact on organizational processes.

**Table 5 table5:** Primary and secondary outcomes and data collection plan.

Outcomes and data source or method					Time point																
					Baseline (T_0_)		Sprints 1 to n						Follow-up								
							T_1_		T_2_		T_n_		T_1 month_		T_3 months_		T_6 months_		T_9 months_		T_12 months_

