### Quantitative Analysis

Quantitative analyses will be conducted using STATA (version 16.0; StataCorp LLC) [55]. Multilevel mixed effects regression models will be used to evaluate any change in primary and secondary outcomes from T_0_ to 12 months after optimization. For clustered longitudinal data, multilevel modeling recognizes that a change in outcome is affected by a fixed effect (ie, implemented changes) and random effects at both individual and group levels and can explicitly account for this multilevel random variation [56].

An a priori power calculation was performed to determine the minimum number of EHRs required to be evaluated to detect a significant change in our primary outcome (ie, data quality measured using DPU, DPO, DPMO, and Sigma level) from T_0_ to 12 months after optimization. First, we used G*Power [57] to compute the required sample size to detect a medium difference (*f*=0.15) at a Cronbach α level of .05 and a power level of .80 using a linear multiple regression analysis with *k*=3 fixed predictors (time, program, and the time × program interaction), which returned a required sample size of 77.

This was multiplied by the anticipated *design effect* [58], which is an adjustment factor for clustering in multilevel models. The design effect is calculated as:

1 + [(*n −* 1) × ICC]                       **(1)**

where n is the expected number of subjects per cluster and “ICC” is the intracluster coefficient or the expected correlation within clusters [58]. We defined a cluster as a facility (ie, site) with a median cluster size of 30 clients per facility. With an anticipated moderate intracluster coefficient of 0.10, the design effect is equal to 3.9, giving a required sample size of 77 × 3.9 = 300. On the basis of the occupancy rates and client population size (n=2200) as of January 2022, our primary outcome analysis will have sufficient statistical power.

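### The minimum of 300 EHRs is wrongly derived: an 8-level program factor and its interaction count as one coefficient each, and the test powered is not the change from T0 to 12 months

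*Protocol article*

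**What the plan says.** The Quantitative Analysis section says the calculation finds how many EHRs are needed "to detect a significant change in our primary outcome" between T0 and 12 months. G*Power was used to "compute the required sample size to detect a medium difference (*f*=0.15"), with a "Cronbach α level of .05 and a power level of .80", in a linear multiple regression with k=3 "fixed predictors (time, program, and the time × program interaction), which returned a required sample size of 77". The design effect is 1 + (30 − 1) × 0.10 = 3.9, which gives 300. The section then concludes that power is sufficient because the client population is 2200. The analysis itself is to be a multilevel mixed effects model.

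On the number of programs, Phase 1.2 says "T_0_ data quality will be measured for each of the 8 programs". Phase 1.3 also says 8, and Table 2 lists 8. The Study Setting text gives a different count: "522 disability services clients across 10 different programs".

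On time, Stage 3 says "Outcomes will be measured at T_0_ and at 1, 3, 6, 9, and 12 months after full optimization". The article does not say how time will be coded.

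On the extent of the audit, Table 3 assigns completeness, currentness and usability to a data warehouse audit of every EHR. Accuracy (ranked first) and clarity are assessed by hand in a random sample, whose size the article does not give.

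**The concern.** Two faults sit in one calculation. First, program is a nominal factor. With 8 levels it uses 7 coefficients, and its interaction with one time term uses 7 more. Entering k=3 is correct only if program is a single numeric or two-level variable, and nothing in the article suggests that. Second, the test behind the figure of 77 asks whether the model as a whole explains any variance. Stable differences between programs would satisfy it even if data quality did not move after optimization. The declared target is change from T0.

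The inputs are also mislabelled, so 77 cannot be reproduced from the text as printed. The value 0.15 is Cohen's f², not f, and Cronbach α is a reliability coefficient, not a significance level.

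At stake is the meaning of 300, the only minimum the article states. Where every EHR is audited it does not bind. Where a sample is drawn by hand, a reader may take 300 as adequate for every term in the model, including program-specific change.

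**Working it through.** **Inputs.** From Quantitative Analysis: effect size 0.15, alpha .05, power .80, k=3, cluster size 30, ICC 0.10, population 2200. From Phase 1.2, Phase 1.3 and Table 2: 8 programs. Assumption: time enters as one term (linear, or T0 versus 12 months).

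**Formula.** Fixed-model multiple regression with u tested coefficients out of p. Power is the probability that a noncentral F with u and N − p − 1 df and noncentrality λ = f²N exceeds the 5% critical value. The required N is then multiplied by 3.9.

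**Reproducing the plan.** With u = p = 3 and f² = 0.15, N = 77 (power 0.802; N = 76 gives 0.796), and 77 × 3.9 = 300.3. Two other readings do not return 77:
- Taking 0.15 literally as f (f² = 0.0225) gives N = 489.
- Testing time alone, 1 df within k=3, gives N = 55.

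So 77 is the 3-df omnibus test with f² = 0.15.

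**Correcting the coefficient count.** 1 (time) + 7 (program) + 7 (interaction) = 15. The effective N at 300 EHRs is 300 / 3.9 = 76.9.

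| Test (f² = 0.15, p = 15) | df | N for 80% | × 3.9 | Power at 300 EHRs |
|---|---|---|---|---|
| Omnibus, as in the plan | 15 | 139 | 542.1 (543) | 44% |
| Time × program | 7 | 104 | 405.6 (406) | 63% |
| Time (stated target) | 1 | 56 | 218.4 (219) | 92% |

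**Sensitivity to what the article leaves open.**
- 10 programs, time as one term (19 coefficients): omnibus 37%, 9-df interaction 56%.
- 8 programs, six occasions as categories (5 + 7 + 35 = 47 coefficients): omnibus 15%, 5-df time test 66%, 35-df interaction 19%.
- The 92% treats 0.15 as the partial effect of time itself. If time's partial f² were 0.02, the 1-df test would have about 23% power at an effective N of 77 and would need 395 × 3.9 = 1540.5 EHRs.

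**All EHRs audited.** 2200 / 3.9 ≈ 564 effective. At f² = 0.15 every test in the table, and every 10-program or categorical-time variant above, exceeds 99% power.

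**The case against.** The strongest reply is that the protocol's conclusion survives. The stated purpose is change from T0 to 12 months. With both faults corrected and 0.15 kept as the effect of time, that test needs about 219 EHRs, fewer than 300. The article calls 300 a minimum and rests adequacy on 2200 clients, and three of the six metrics are audited on all EHRs. This stands, and it limits the consequence.

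It also rules out a stronger reading that a reader might draw, namely that the study has 44% power instead of 80%. That figure belongs only to the 15-df omnibus test, which is not the hypothesis of interest.

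A second reply is that no power is promised for program-specific change. The Phase 1.2 sentence about programs concerns describing baseline variation. This also stands: 63% is not a breach of a stated goal. But time × program is a named model term, and a reader may assume that 300 covers it.

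Third, the article nowhere sets the manual-audit sample at 300, so that link is conditional.

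Fourth, a fixed regression times a design effect is not the power of a multilevel model with repeated measures. It also depends on how records are spread. As an assumption, 300 EHRs spread evenly over the 24 sites listed in Table 2 would be 12.5 per site. The design effect is then 1 + 11.5 × 0.10 = 2.15, the effective N is about 140, and the 15-df omnibus test has about 80% power. The percentages are therefore like-for-like corrections of the plan's shortcut and no more.

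None of these replies defends k=3 or the choice of the omnibus test.

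**Conclusion.** The derivation of 300 is wrong as written, on two counts: 3 coefficients are counted where the named model has 15, and an omnibus R² test stands in for the test of change from T0. On the plan's own method, power at 300 EHRs is about 44% for the corrected omnibus test, about 63% for time × program and about 92% for the 1-df time contrast. The requirements are about 543, 406 and 219.

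These figures assume 8 programs, time as one term, f² = 0.15 for whichever term is tested, and a design effect of 3.9. They are not the exact power of the multilevel model.

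The documents do not support saying that the primary comparison is underpowered. The time contrast is covered at 300 under the plan's effect size, and the metrics audited on all EHRs are amply powered. The practical weight falls on accuracy and clarity, and on program-specific claims, if the manual sample is near 300. This should be corrected, but it does not undermine the study.

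**What to change.** In Quantitative Analysis:
- Drop the k=3 omnibus figure.
- State the calculation for the T0 versus 12-month time contrast: 56 × 3.9 ≈ 219 under the present inputs. Say how time is coded, and that 0.15 is taken as the effect of time itself.
- Report separately what the time × program test needs: 104 × 3.9 ≈ 406. If the sample is not sized for it, describe program-specific change as exploratory.
- Write f² = 0.15 in place of f = 0.15, and significance level .05 in place of Cronbach α.
- Reconcile the program count (10 in the Study Setting text, 8 in Table 2 and in Phases 1.2 and 1.3), because it sets the degrees of freedom.
- Judge the manual-audit sample for accuracy and clarity against the restated figures.

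The cost is a rerun of the calculation and some rewording. No new clients are needed, because about 2200 EHRs are available. The only possible extra work is a larger manual audit, if program-specific change in accuracy or clarity is to be tested rather than described.

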**Disability**				
	TRP^f^	1	53	Specialist neurorehabilitation service for people aged 18-65 years with acquired brain injury
	TAP^g^	1	23	Short-term, posthospital support and active management for people aged 18-65 years with disability
	SIL^h^	8	71	Long-term and permanent high care accommodation for people aged 18-65 years with disability
	CAPB^i^	—	375	Home-based support for people aged 18-65 years with disability and NDIS^j^ funding

^a^RAC: residential aged care.

^b^SDCP: Specialist Dementia Care Program.

^c^TCP: Transitional Care Program.

^d^AH: at home.

^e^AH and CAPB services are at-home and community-based care sites.

^f^TRP: Transitional Rehabilitation Program.

^g^TAP: Transitional Accommodation Program.

^h^SIL: Supported Independent Living.

^i^CAPB: capacity building.

^j^NDIS: National Disability Insurance Scheme.

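### The design effect of 3.9 and the required 300 EHRs rest on a median facility size; on Table 2's totals the same formula gives about 400 to 527, and the comparison with n=2200 does not establish power

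*Protocol article*

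**What the plan says.** The sample-size paragraph under Quantitative Analysis has four steps.

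- An unclustered requirement comes from a multiple-regression calculation with three "fixed predictors (time, program, and the time × program interaction), which returned a required sample size of 77".
- A design effect of 1 + (n − 1) × ICC is applied, "where n is the expected number of subjects per cluster".
- The value entered is a median: "We defined a cluster as a facility (ie, site) with a median cluster size of 30 clients per facility". Then: "With an anticipated moderate intracluster coefficient of 0.10, the design effect is equal to 3.9, giving a required sample size of 77 × 3.9 = 300".
- The 300 is set against a client population of 2200 as of January 2022, and the paragraph concludes that "our primary outcome analysis will have sufficient statistical power".

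Table 2 gives sites and clients by program. Six programs have a site count. The two home-based programs, at home (AH, 1000 clients) and capacity building (CAPB, 375 clients), have a dash there, with the footnote "AH and CAPB services are at-home and community-based care sites".

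In Table 3, completeness, currentness and usability are audited on all EHRs. Accuracy and clarity are assessed on random samples whose size is not given.

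**The concern.** There are two separate problems.

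First, the n in the formula is an expected cluster size, and a median is not that. Program averages run from about 9 clients per site (SIL) to about 68 (RAC). With sites this unequal, a median can sit well below the mean, and the mean itself understates the variance inflation. Too small an n gives too small a design effect and too small a required N.

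Second, the requirement is built on facilities, but the population offered as proof of power is not. If Table 2's facility total of 1029 applies, a population of 2200 must include at least 2200 − 1029 = 1171 home-based clients, for whom no cluster is defined. Under clustering, moreover, a raw client count says little about power, because each cluster's contribution is capped.

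The 300 matters in practice. It is the only minimum number of EHRs in the article, so it is the natural target for the sampled accuracy and clarity audits, and accuracy is the top-ranked metric.

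**Working it through.** **Inputs.** Quantitative Analysis: alpha 0.05, power 0.80, effect size 0.15, three predictors, ICC 0.10, median 30. Table 2 (sites, clients): RAC 11, 750; SDCP 1, 31; TCP 2, 101; TRP 1, 53; TAP 1, 23; SIL 8, 71; AH 1000 and CAPB 375 with no site count.

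**1. The plan's own figures.** The overall F test in linear regression (3 and N − 4 degrees of freedom, noncentrality f² × N) with f² = 0.15 gives N = 77. The 0.15 has to be read as f²: taken literally as f, it would give 489. Then 1 + 29 × 0.10 = 3.9 and 77 × 3.9 = 300.3. The stated arithmetic reproduces.

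**2. Mean facility size.** Sites: 11 + 1 + 2 + 1 + 1 + 8 = 24. Clients: 750 + 31 + 101 + 53 + 23 + 71 = 1029. Mean: 1029 / 24 = 42.9, however clients are split among sites.

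**3. Size-weighted mean, Σm²/Σm.** With equal sites within each program, Σm² = 750²/11 + 31² + 101²/2 + 53² + 23² + 71²/8 = 51136 + 961 + 5101 + 2809 + 529 + 630 ≈ 61166, and 61166 / 1029 = 59.4. Unequal sites within a program can only raise Σm², so this is a lower bound.

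**4. Design effect, required N, and power of 300 EHRs (ICC 0.10).**

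| Cluster size | Design effect | 77 × design effect | Power of 300 |
|---|---|---|---|
| 30 (plan) | 3.90 | 300 | 0.80 |
| 42.9 (mean) | 5.19 | about 400 | 0.66 |
| 59.4 (size-weighted) | 6.84 | about 527 | 0.52 |

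The power column evaluates the same F test at 300 divided by the design effect, so it assumes whole facilities are audited.

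**5. Could the median really be 30?** Yes. Take eight SIL sites near 9, TAP 23, SDCP 31, TCP 50.5 twice, TRP 53, three RAC sites of 29 and eight RAC sites averaging (750 − 87) / 8 = 82.9. The median is then exactly 30. The mean is still 42.9 and the size-weighted mean rises to 65.6, giving a design effect of 7.46 and N of about 574.

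**6. Clients outside the cluster definition.** (1000 + 375) / 2404 = 57%.

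**7. Effective sample if every EHR is audited.** In a mixed model a cluster of size m contributes m / (1 + (m − 1) × ICC), which cannot exceed 1/ICC, or 10 at ICC 0.10. Summing over clusters, with equal sites within program:

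| ICC | 24 facilities only | Plus AH and CAPB, each assumed to be one cluster |
|---|---|---|
| 0.05 | 290 | 329 |
| 0.10 | 177 | 197 |
| 0.20 | 102 | 112 |

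The unclustered requirement is 77. Power is 0.995 for 177 and 0.91 for 102. By contrast, dividing the stated population by the stated design effect would suggest 2200 / 3.9 = 564.

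**The case against.** The strongest reply is that the conclusion survives. About 400 and about 527 are both below the 1029 facility clients, and the effective sample exceeds 77 across ICC 0.05 to 0.20 even with home-based clients left out. That stands. A reader might infer that the study is underpowered; the documents do not show it. Only a further assumption reverses the result: treating AH and CAPB as one cluster each and applying a single size-weighted design effect to everyone (50.9, N about 3919, more than the 2404 clients). The article states no such structure, and the mixed-model effective sample under the same assumption is still about 197.

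A reader might also infer that a median of 30 contradicts Table 2. It does not. Table 2 gives program totals only, and step 5 shows a configuration with that median. Table 2 and the population of 2200 may also reflect different counts, since 2200 is tied to occupancy and Table 2 sums to 2404. But a true median of 30 does not rescue 3.9, because on Table 2's totals the mean stays at 42.9.

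Third, n can be read as records sampled per site rather than facility size. Spread evenly over 24 sites, 300 EHRs are 12.5 each; the design effect is 1 + 11.5 × 0.10 = 2.15, the effective sample 300 / 2.15 = 140, and power about 0.98. This is correct, and it limits the shortfall to audits of whole facilities. The article describes no such allocation, however, and itself uses facility size as n.

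Finally, how home-care clients are grouped could be left to a fuller document. That is fair as to detail, but this article both defines the cluster as a facility and relies on a population that must include home-based clients.

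**Conclusion.** The stated design effect and required N are too low on the plan's own formula and Table 2's totals: at least 5.19 and about 400, and 6.84 and about 527 with the size-weighted mean, against 3.9 and 300. That is an increase of about 33% (400/300) to 76% (527/300). This assumes that n is full facility size, as the article uses it, that ICC is 0.10, and that the F test with f² = 0.15 is accepted as given. The 59.4 is a lower bound.

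The sentence on 2200 does not establish power, because it sets a facility-based requirement against a population that includes home-based clients and takes no account of the cap per cluster. The conclusion it draws probably still holds for a full audit. The error therefore lies in the stated figure and its justification. It has most consequence for the sampled manual audits, where 300 could be taken as the target without a plan for spreading it over sites.

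**What to change.** - Recompute the design effect from the actual site list with the size-weighted mean. For the sampled accuracy and clarity audits, use the planned number of EHRs per site instead, and state that number.
- Restate the required N on that basis.
- Name the cluster unit for AH and CAPB, for example the care team or region that does the documenting, or treat the two programs as a separate stratum.
- Replace the sentence on 2200 with the effective sample size from the facilities plus the home-care clusters, over ICC 0.05 to 0.20, set against 77.

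The cost is one recalculation from a list the organization already holds and one rewritten paragraph. The downside is that the stated required N becomes less favourable.

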### Qualitative Analysis

Qualitative data from user interviews and surveys will be coded and analyzed using NVivo 12 (QSR International) [59]. An inductive thematic analysis approach will be used to identify and understand key themes, specifically to classify, order, and reassemble data to identify converging and diverging perspectives. A total of 50 interviews are anticipated to reach saturation.

## Results

As of June 1, 2022, stage 1 commenced with T_0_ data quality audits conducted to identify the current data quality and system strengths and limitations. T_0_ data quality audits will be followed by user consultations to identify root causes of data quality issues. Clinical information requirements will be developed by May 2023 to inform optimization (stage 2) and evaluation (stage 3). Results are expected to be published in June 2023.

## Discussion

It is anticipated that the study findings will show that optimization of clinical data and documentation will, in turn, have a major impact on care delivery and clinical outcomes and reduce business costs. Although the aim of the OPTIMISE study is to build internal organizational capacity for continuous improvement of clinical data quality, the findings will also be important to individuals and organizations across the aged care and disability service sector, as well as the wider health care sector, which is seeking novel technology solutions to improve the quality of clinical data to support high-quality care delivery and operational efficiency. In addition, the findings will be relevant to researchers and organizations interested in learning the opportunities and limitations of engaging an Agile LSS framework for quality improvement in a health care setting. These findings can stimulate organization-level research to support the development of evidence-based care. The findings will also be disseminated nationally and internationally through industry presentations, scientific conference presentations, and peer-reviewed journal publications.

